### Recruitment

2.6

Recruitment of the participants began in September 2019 and is expected to finish in March 2021. Before inviting participants to sign the informed consent form, information on the study goals and procedures will be provided verbally. The participants will also be invited to raise questions or doubts on any aspect of the study. Data confidentiality guarantees will be provided to participants by the principal investigator. Written consent will be obtained from all participants before registration, and participants may withdraw from the trial at any point in time without penalties. The written consent form includes information regarding the background and purpose of the study, therapeutic interventions, outcomes, and the expected benefits and drawbacks.

### Randomization and blinding

2.7

Participants will be randomly allocated to the 2 groups through a sequence of numbers generated by a computer program before starting the selection process. The group assigned to each patient will be kept in a sealed envelope with the objective of concealing the assignment to the researcher, who will decide on the entry of subjects to the study (Fig. 3). Given the nature of the interventions, the physiotherapists, and the patients, blinding will not be possible. However, the evaluator and statistician will be blinded to which group the subjects evaluated will belong.

**Figure 3 F3:**
[figure not shown]
Flow diagram of patients through phases of clinical study.

### Data management

2.8

Information obtained from the evaluation of each participant will be recorded on a paper print-out. The information will then be handwritten on a paper document case report form and entered into an Excel file for future statistical analyses. In accordance with the Personal Information Protection Act, the names of all participants will not be disclosed, and a unique identifier number given during the trial will be used to identify participants. All of the participants will be informed that the clinical data obtained in the trial will be stored in a computer and will be handled with confidentiality. The participants’ written consent will be stored by the principal investigator.

### Statistical analysis

2.9

The continuous variables will be presented as means and standard deviations, and categorical variables as number and percentage. To determine whether parametric statistical tests are appropriate for use in data analysis, the fitting to normal distribution will be evaluated using both statistical (Shapiro–Wilk test) and graphical (normal probability plot) methods. To examine baseline differences of the 2 groups, a 1-way analysis of variance (for continuous variables) and Chi-square tests (for categorical variables) will be conducted. Repeated measures analysis of covariance will be performed on outcome variables, with point of measurement (3 levels: preintervention, 6 weeks postintervention, and 12 weeks postintervention) as the within-subject factor and with type of intervention (2 levels: supervised early exercise program in combination with standard treatment versus standard treatment alone). The covariates were baseline values of each outcome variable.

Data will be processed independently by 2 researchers, and inconsistences will be detected using the VALIDATE command of Epi Info (CDC) software. After checking the truthfulness of outliers and extreme values, these will be winsorized using below the 1st percentile and above the 99th percentile of the distribution of variables. Before conducting the study, and after considering the nature of the missing data in patients with incomplete entries, these will be imputed using chained equations.

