### Outcome measures

2.4

Baseline and postintervention outcome variables and potential confounders will be measured in both the intervention and control groups. Measurements will be performed before surgery, after 6 weeks, and the end of the program (12 weeks).

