### Sample size calculation

2.5

The sample size for this trial is based on an expected mean difference between groups of 11 points of the Constant–Murley questionnaire, which is the minimum clinically important difference.^[86]^ The mean assumed for the calculation was 63.3 with a standard deviation of 15 points based on results of other randomized clinical trials.^[87]^ To detect this difference between both treatments, with a value of *α* = 0.05 (probability of committing a type I error) and a statistical power of 95%, a minimum of 49 patients per group is needed. This minimal sample size estimate has been increased by 20% after considering the potential dropouts, finally including 58 patients for each group. Accordingly, the proposed experimental hypothesis is that there will be a difference of at least 11 points in the Constant–Murley questionnaire in the intervention group versus the control group. The sample size was determined using the Stata SE software, version 15 (StataCorp, College Station, TX).

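### The pre-surgery score is both an outcome level and the covariate; if the effect is read from the group term, 11 points at both visits is reported as 7.3

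*Protocol article*

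**What the plan says.** The protocol article, Outcome measures (2.4), sets three assessments: "Measurements will be performed before surgery, after 6 weeks, and the end of the program (12 weeks"). Statistical analysis (2.9) applies a repeated measures analysis of covariance to the outcome variables, "with point of measurement (3 levels: preintervention, 6 weeks postintervention, and 12 weeks postintervention) as the within-subject factor", with intervention group as a two-level factor. It then states: "The covariates were baseline values of each outcome variable".

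Sample size calculation (2.5) rests on an "expected mean difference between groups of 11 points of the Constant–Murley questionnaire", which it calls the minimum clinically important difference. It adds: "The mean assumed for the calculation was 63.3 with a standard deviation of 15 points". The result is "a statistical power of 95%, a minimum of 49 patients per group is needed". The hypothesis is that "there will be a difference of at least 11 points" in favour of a group contrast, with no visit attached.

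**The concern.** One measurement sits on both sides of the model. A patient's pre-surgery score is the first of the three repeated outcomes and also the adjustment variable. Adjusted for itself, it can show no treatment difference, so any group effect averaged over the three levels includes a built-in zero.

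This matters because the trial's hypothesis concerns the size of a difference, not only its existence. An effect exactly at the 11-point threshold could be reported as falling short of it. The same data could give 7.3 or 11 points depending on which term of the fitted model is read. This is a model stated in the text, not a detail left for later, and it applies to every outcome including the primary one.

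**Working it through.** **Inputs.** From section 2.5: difference 11, SD 15, alpha 0.05, power 95%, 49 per group. From section 2.9: three outcome levels and a baseline covariate. The protocol gives no correlations between visits, so those below are assumptions.

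**The plan's own figure.** Two-sided, n = 2 × 15² × (1.960 + 1.645)² / 11² = 450 × 12.995 / 121 = 48.3, so 49 per group. This matches. With 49 per group the power is 95.3%. The trial is thus sized for one simple two-group difference.

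**Group term, three levels.** Write Y0, Y6 and Y12 for the scores, and d6 and d12 for the adjusted group differences. Regressing Y0 on group and Y0 gives a group coefficient of 0 and residuals of 0. Least squares is linear in the outcome, so for the mean of the three levels:

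- group effect = (0 + d6 + d12)/3 = (2/3) × (d6 + d12)/2
- residual = (0 + e6 + e12)/3 = (2/3) × (e6 + e12)/2

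Estimate and standard error both shrink by 2/3 relative to the two-visit average, so t and p do not change.

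| True benefit at 6, 12 weeks | Three-level group term | Mean of 6 and 12 weeks | 12-week contrast |
|---|---|---|---|
| 11, 11 | 22/3 = 7.33 | 11.0 | 11.0 |
| 5.5, 11 | 16.5/3 = 5.5 | 8.25 | 11.0 |
| 0, 11 | 11/3 = 3.67 | 5.5 | 11.0 |

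Check with all correlations at 0.5. The residual variance of the two-visit mean is 225 × 1.5/2 − 225 × 0.25 = 112.5, so SE = √(112.5 × 2/49) = 2.14. The three-level SE is 2.14 × 2/3 = 1.43. Both give t = 5.13 (11/2.14 and 7.33/1.43). Simulation (2,000 trials, 49 per group) gave SEs of 2.15 and 1.43, 99.9% power in both, and an adjusted baseline difference of exactly 0 in every trial.

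**Group-by-time term, covariate not crossed with time.** The covariate adds the same amount at each level and cancels from Y6 − Y0 and Y12 − Y0. The test is then an unadjusted change-from-baseline comparison. For the 12-week difference, its variance relative to a baseline-adjusted 12-week analysis is 2(1 − ρ)/(1 − ρ²) = 2/(1 + ρ), which is 1.54 at ρ = 0.3, 1.33 at 0.5 and 1.18 at 0.7. Simulated power:

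| Assumed correlations (baseline to follow-up / 6 to 12 weeks) | 11 at both | 5.5 then 11 | 12-week ANCOVA |
|---|---|---|---|
| 0.3 / 0.6 | 89–90% | 81–82% | 96% |
| 0.5 / 0.6 | 97.5% | 91.3% | about 98% |
| 0.6 / 0.7 | 99.0% | 97.4% | about 99% |

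With a 12-week-only benefit at 0.3/0.6 this test has about 95% power, so there the loss is negligible.

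**12-week contrast, covariate crossed with time.** Regressing Y12 − Y0 on group and Y0 gives a group coefficient of d12 − 0 and the residual e12. That is the 12-week ANCOVA exactly: 11.0 points with the same t, and power of 96% to over 99% for ρ from 0.3 to 0.7.

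**The case against.** The strongest reply is that section 2.9 never says the group main effect is the number to be reported. That stands. The shrinkage is conditional on reading that term, and the same three-level model can yield an undiluted 12-week contrast.

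A reader might also infer that the double use of baseline costs the main-effect test its power. It does not, since t is identical with or without the baseline level. For a benefit at 12 weeks only, main-effect power at 0.3/0.6 is about 56% with three levels and the same with two. The loss comes from averaging in week 6. Likewise, of the 11 − 3.67 = 7.33 points missing in that case, 5.5 are due to week 6 and only 5.5 − 3.67 = 1.83 to the baseline level.

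The lower group-by-time power depends on correlations the protocol does not give, and it shrinks as they rise. The test itself is valid under randomisation, and no inflation of false positives was found.

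Two further inferences do not hold. Describing the visits as weeks after the intervention is loose labelling: the Abstract and section 2.4 fix them as before surgery, 6 weeks and 12 weeks, so no analysis changes. A condensed article may also leave the decisive contrast to a fuller document. What remains is the model as written, which is stated and wrong.

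**Conclusion.** The specification in section 2.9 is faulty and should be corrected before analysis. If the effect is taken from the group term, its size is (d6 + d12)/3: 11 points at both visits reads as 7.3, one third below the trial's threshold, with an unchanged p-value. This is exact algebra for complete data and needs no assumed correlation. If the group-by-time term is used with an uncrossed covariate, the cost is the benefit of adjustment: 82–90% power against 96% at assumed correlations of 0.3/0.6, and little at 0.6/0.7. A 12-week contrast with the covariate crossed with time carries no cost. The documents do not support saying that the trial will report a diluted effect, only that the stated model allows it. The weak power for a 12-week-only benefit is a reason to name the visit, not a consequence of using baseline twice.

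**What to change.** In section 2.9, make the within-subject factor two levels, 6 and 12 weeks, with baseline and baseline by visit as covariates. Alternatively, keep three levels with a common baseline mean for both groups and drop the baseline covariate. Either removes the defect, and no change of model family is required. Then state that the 11-point hypothesis is read from the adjusted between-group difference at a named visit, for example 12 weeks as the end of the program, and not from an average over visits. The cost is two sentences, with no new data and no change to the sample size.

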#### Potential confounders

2.4.3

Comorbidities: comorbidities that affect RC healing and postoperative outcomes such as hypercholesterolemia,^[16,80]^ diabetes,^[81–83]^ and smoking^[84,85]^ will be registered.

Clinical variables: the affected dominant shoulder, duration of symptoms (months), and previous treatments received in the last 3 months (supervised physical therapy, exercises only, use of paracetamol/nonsteroidal anti-inflammatory drugs, and use of opioids) will be registered.

Anthropometry and body composition: Weight will be measured with the patient barefoot and in light clothing. Height will be measured using a wall stadiometer, with the patient barefoot and upright and with the sagittal midline touching the back board. Body mass index will be calculated as weight in kg divided by the square of the height in meters.

Socio-economic status: Education level will be classified as primary education (functionally illiterate, without any studies, or those who have not completed primary education), middle education (primary education, high school/secondary, or baccalaureate education), and university education (college or PhD degree). Occupation will be categorized as heavy load, light load, and sick leave in the last month.

Daily movement behavior (DMB): defined as a construct including; physical activity, sedentary behaviors and sleep time. DMB will be measured by using the Xiaomi MI Band 3 Smart Bracelet, which provides information on physical activity (steps per day), sleep time, and sedentary time.

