## Discussion

3

The aim of this article is to describe the rationale and methods of a randomized controlled trial to test the effectiveness of 2 exercise programs in adult with arthroscopic RC repair. The control group will receive a standard exercise program based on a consensus statement on shoulder rehabilitation developed by the ASSET.^[45]^ The intervention group will receive a supervised early exercise program in combination with standard treatment. This supervised exercise program will be based on EMG evidence.

Despite the high incidence of surgery for RC repair, there is no consensus on the most effective approach for postoperative rehabilitation^[89,90]^ due to available evidence on timing and the load on the recovery process of tendon healing.^[34]^ Studies have shown that early motion increases ROM after RC repair^[37–41]^; however, the risk of re-tear is significantly higher compared with immobilization.^[38,39,42]^ Additionally, immobilization can result in shoulder stiffness, pain, functional limitations, and frustration for patients.^[43]^ Therefore, it is difficult to take a clinical decision about the best rehabilitation program. Nevertheless, the influence of these protocols on tendon healing and functional outcome is not well known.^[91–93]^

Usually, orthopedic surgeons prescribe a short period of immobilization and early passive mobilization to minimize stiffness; however, the type of immobilization, position, and shoulder motion remain unclear for tendon healing.^[42,94,95]^ Second, a home exercise program has not been developed, because factors such as age, tobacco use, comorbidities, and intrinsic tendon characteristics can be confounding factors for prescribe a home exercise program.^[40,42,95]^

Currently, strict immobilization time ranges from 0 to 6 weeks, where exercises are not prescribed to protect the surgery.^[90]^ Evidence needs from protocols describing important characteristics of a supervised early exercise program such as; an indirect and low load neuromuscular activation of the RC muscles, according to previous EMG studies, the load is less than 20% MVIC without overloading the repaired tendon.^[44,45,47,48]^ This protocol also describes other characteristic, a short duration isometric contraction muscular without compressive load in tendon, with a hypoalgesic action.^[96]^

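### The outcome model adjusts for the baseline score alone, while three recorded comorbidities said to affect outcome are only described and tested between arms: a modest loss of efficiency, not a validity problem

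*Protocol article*

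**What the plan says.** Section 2.9 (Statistical analysis) specifies a repeated measures analysis of covariance and closes its covariate set: "The covariates were baseline values of each outcome variable". The same section has the arms compared at the start: "To examine baseline differences of the 2 groups, a 1-way analysis of variance" for continuous variables, with chi-square tests for categorical ones.

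Section 2.4.3 (Potential confounders) registers "comorbidities that affect RC healing and postoperative outcomes such as hypercholesterolemia", followed by diabetes and smoking. It also registers symptom duration, dominance, previous treatment, anthropometry, education, occupation and daily movement. No section gives any of these a place in the outcome model. Section 2.7 describes a computer-generated sequence and mentions neither stratification nor minimisation.

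**The concern.** The article itself fixes both the covariates and the baseline tests, so this is not a detail left to an unseen analysis plan. The protocol says that three comorbidities influence outcome and then uses them neither in the described allocation nor in the model.

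The one job they are given is of little use. Under randomisation every baseline difference is due to chance, so the test addresses a null hypothesis already known to be true. A non-significant result does not show that an imbalance is harmless, and a significant one is likely somewhere in a long table.

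At stake are some precision, and some protection against a chance imbalance in factors that the protocol regards as prognostic.

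**Working it through.** **Inputs from section 2.5.** The target is "an expected mean difference between groups of 11 points of the Constant–Murley questionnaire". The spread is given as "The mean assumed for the calculation was 63.3 with a standard deviation of 15 points". Alpha is 0.05, power is 95%, and the stated minimum is 49 per group.

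**Assumed, because the documents give no figure.** The baseline-outcome correlation r is taken as 0.25 to 0.5. R² is the share of the variance left after the baseline score that the added factors explain, taken as 5% to 15%.

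**1. The plan's own figure.** n = 2 × (1.960 + 1.645)² × 15² / 11² = 48.3, so 49 per group, two-sided. A one-sided test would need 41. The stated figure reproduces. It uses the raw SD and takes no credit for any covariate. SE = 15 × √(2/49) = 3.03. Power = Φ(11/3.03 − 1.96) = 95.3%, or 94.9% by the t distribution.

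**2. The planned model.** Adjusting for the baseline score multiplies the SE by √(1 − r²). At r = 0.25 the SE is 2.93 and power 96.3%. At r = 0.5 they are 2.62 and 98.7%. This is the right starting point for judging further covariates.

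**3. Added factors.** They multiply the SE by √(1 − R²): 0.975 at 5%, 0.949 at 10% and 0.922 at 15%. These are falls of 2.5%, 5.1% and 7.8%.

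**4. Degrees-of-freedom cost.** With N = 98 and q added terms, the variance rises by about (N − 3)/(N − q − 3). For q = 3 this is 95/92 = 1.033 (SE × 1.016). For q = 5 it is 95/90 = 1.056 (SE × 1.027). Break-even R² is q/95: 3.2% for three terms and 5.3% for five.

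**5. Net result, 49 per group, normal approximation.**

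| Added terms | R² | SE relative to planned model | Power, r = 0.25 | Power, r = 0.5 |
|---|---|---|---|---|
| none | – | 1.000 | 96.3% | 98.7% |
| 3 | 5% | 0.990 | 96.6% | 98.8% |
| 3 | 10% | 0.964 | 97.3% | 99.2% |
| 3 | 15% | 0.937 | 97.9% | 99.4% |
| 5 | 5% | 1.001 | 96.3% | 98.7% |
| 5 | 10% | 0.975 | 97.0% | 99.0% |
| 5 | 15% | 0.947 | 97.7% | 99.3% |

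**6. Chance imbalance.** For a binary factor with assumed prevalence p of 20% to 40%, the 95% limits of the between-arm difference are 1.96 × √(2p(1 − p)/49), or 15.8 to 19.4 percentage points. A chi-square test at 5% passes anything smaller. If the factor is worth an assumed 5 to 10 points, a difference at those limits moves the estimate by 5 × 0.158 = 0.8 to 10 × 0.194 = 1.9 points. That is near the worst case.

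Conditional on an imbalance of z standard deviations in the omitted factors, the test statistic under the null is √R² × z + √(1 − R²) × Z, with Z standard normal. At z = 1.9, type I error is 6.5% for R² = 5% and 7.9% for 10%. At z = 1 it is about 5%. Averaged over randomisations it is 5%.

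**7. Baseline tests.** With k independent tests, the chance of at least one result at p < 0.05 is 1 − 0.95^k: 34% for k = 8 and 46% for k = 12. Counting the listed factors and the outcomes at baseline gives about 25 variables and 72%. Many of these are correlated (weight, height and body mass index, for example), so 72% overstates it.

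**The case against.** The strongest reply is that nothing here is wrong. A prespecified analysis of covariance on the baseline score is unbiased in a randomised trial and holds its 5% error rate, and chance imbalance in other factors is already reflected in the standard error. Further covariates are a matter of choice. This stands, and it limits the point to efficiency and conditional imbalance.

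Several stronger readings are tempting but not supported:

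- **That adjustment is needed to restore 95% power after dropout.** With 47 completers per arm (58 × 0.8 = 46.4, rounded up) and the raw SD, power is about 94.5% by normal approximation. The planned model is not the raw comparison, however. It already reaches about 96% at r = 0.25 and 98.4% at r = 0.5.
- **That the Discussion calls age and tendon characteristics confounders of the comparison.** The words "factors such as age, tobacco use, comorbidities, and intrinsic tendon characteristics can be confounding factors" belong to a sentence about prescribing home exercise. Section 2.4.3 carries the point alone.
- **That tear size should be added at no cost.** It serves as an eligibility limit and is not among the variables registered in section 2.4.3.
- **That confounders are re-measured after treatment and then adjusted for.** Section 2.4 says "Baseline and postintervention outcome variables and potential confounders will be measured in both the intervention and control groups", which can mean that only the outcomes are measured twice. The schedule figure is not available, and the plan never uses post-intervention movement data as a covariate.
- **That covariates will be chosen from the baseline p-values.** No passage links the tests to any such choice.

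**Conclusion.** The point holds as a modest improvement. The plan gives three comorbidities that it calls outcome-relevant no role in the outcome model, and it relies on baseline tests that cannot correct imbalance. The estimate and the overall error rate are sound.

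The gain is a 2.5% to 8% smaller standard error before the degrees-of-freedom cost. With three added terms it is about 1% to 6% net, and with five it runs from nothing to about 5%. Power rises by at most about 1.6 percentage points from a level already above 95%. These figures rest on assumed values of r and R². If the factors explain less than about 3% of the remaining variance, adding three terms gains nothing. The case for dropping the baseline significance tests does not depend on these assumptions.

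**What to change.** In section 2.9:

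1. Replace the covariate sentence with a prespecified set: the pre-surgery value of the outcome analysed plus diabetes, smoking and hypercholesterolemia, included whatever balance is observed. Age and symptom duration may be added, if named in advance. Keep the model with the baseline score only as a sensitivity analysis.
2. Remove the ANOVA and chi-square comparisons of the arms at baseline, and present that table descriptively.

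The change should be made before unblinding. Section 2.4.3 already registers the three comorbidities and symptom duration, so no visits or patients are added. The cost is three to five degrees of freedom and the need for these pre-surgery fields to be complete.
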